#### Independent variables

Data will be captured on preoperative independent variables such as gender, age, ASA level, and degrees of the hemorrhoids.

### Consent

Any patient with third- and/or fourth-degree hemorrhoids aged above 18 years is eligible for this study and will be given an equal chance to participate and will be consented to by the principal investigator at the time of screening for eligibility.

### Randomization and blinding

After fulfilling the enrollment criteria and obtaining the informed consent, the participants will be allocated randomly by assistant researchers well trained to either the local anesthesia group (group A) or the saddle block group (group B) by using envelope allocation concealment whereby half of the envelopes will contain a chit with letter A while the other half will have a chit with letter B signifying local anesthesia and saddle block, respectively. The content of the envelope will be opened once the patient is in the theater, and the patients and outcome assessors will be blinded about the anesthesia.

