**Methods:**

The protocol for a prospective equivalence randomized, double-blind controlled trial was conducted among patients with primary uncomplicated 3rd- or 4th-degree hemorrhoids. Recruitment was started in December 2021 and is expected to end in May 2022. Consenting participants who require open hemorrhoidectomy indicated at Kampala International Teaching Hospital, Uganda, will be randomized into two groups of 29 patients per arm.

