According to a similar randomized control trial that compared open hemorrhoidectomy under local anesthesia versus supine anesthesia at the Korle Bu Teaching Hospital in Ghana [16], the difference in the mean pain scores between the 2 groups was *δ* = 0.73; pooled standard deviation in the mean pain scores *S* = 1.9 (average of 2.356 for local anesthesia and 1.479 for supine anesthesia), an estimated sample size of 104 participants per group, was obtained. Since at the time of the proposed study, nothing was known about the mean pain score following OH under local anesthesia and the real difference in clinical outcome between the two techniques in Uganda, the sample size was adjusted using Slovin’s formula as detailed by Ellen [17] based on the hospital records, Kampala International University Teaching Hospital which registered an average of 33 cases of grade 3 or 4 hemorrhoids in a period of 6 months that corresponded to the intended data collection period; thus, a sample size of 26 participants per group was obtained which was increased to 29 participants in each arm, based on a rate of 10% in each arm to compensate for the loss to follow-up and non-responsiveness found.

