#### Participant recruitment and study procedure

Participants will be recruited from surgical outpatient by trained research assistants. Patients with uncomplicated 3rd- or 4th-degree hemorrhoids will be assessed for study eligibility using a screening log. Written informed consent will be obtained from the eligible participants.

The patients admitted for elective hemorrhoidectomy will undergo pre-anesthetic evaluation the day before surgery and will be given fasting guidelines including 6 h for solid foods and 2 h to anesthesia for clear fluids like water. All patients will receive prophylactic antibiotics (intravenous 500 mg of metronidazole) within 60 min prior to incision [18]. Two hours before surgery, the patient will be receiving an enema intrarectal. All patients scheduled for surgery will be informed and admitted a day prior to surgery, prepared, and included in the theater program in order to maintain continuity of care.

Once in the operating room, vital signs will be taken (blood pressure, pulse rate, oxygen saturation, and monitoring of the ECG). Co-loading of intravenous crystalloids, namely normal saline and or ringers’ lactate, will be done using a restrictive approach of fluid administration and undergo open hemorrhoidectomy under saddle block [19].

Aseptic protocols will be observed for all groups. Group A patients, in lithotomy or prone jack-knife positions, will be infiltrated with bupivacaine 0.5% at a maximum safe dose of 2 mg/kg with adrenaline (1:200,000) following the technique of Jinjil et al. [20]. The local anesthetic mixture will be administered by the principal investigator as follows: The first two injections will be applied bilaterally (1 and 4), 5 mm from the border of the perianal skin, and the mixture will be injected at 12 and 6 o’clock (3 ml each side). Thereafter, further 4 injections will be administered into 4 quadrants performing a diamond shape (2, 3, 5, and 6), 5 mm from the anal opening; every 1 ml will be injected at a 4-cm, 3-cm, and 2-cm depth from the skin, respectively, as shown in Fig. 1.

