**Fig. 1 Fig1:**
[figure not shown]
Local anesthesia infiltration [20]

With this technique, the mixture will fill the inter-sphincteric space and block the inferior rectal branch of the pudendal nerve (S2, S3) and the perineal branch of the 4th sacral nerve, causing paralysis of the external sphincter.

For group B patients, the back will be cleaned with 70% alcohol and draped while in a sitting position. The anesthetist or the anesthesiologist will identify the L4/L5 interspace by anatomical landmarks. Lidocaine will be infiltrated in the skin and subcutaneous tissue to form a wheel in the skin. A 25-G quincke spinal needle will be introduced into the sub-arachnoid space using either the midline or paramedian approach as deemed necessary by the anesthetist. Once the free flow of cerebrospinal fluid is observed in the hub of the needle, 1.5 ml of 0.5% bupivacaine will be administered. The patient will be kept in the sitting position for 10 min and thereafter placed in supine. Time 0 will be reordered once the cleaning of the back starts.

After the proof of the effect of anesthesia is administrated, participants in both groups will be put in lithotomy position, and the perianal region will be cleaned and draped before the beginning of open hemorrhoidectomy which will be done by the principal investigator. The technique for open hemorrhoidectomy will be as described by Milligan Morgan Clinic [21] after which dressing will be done, and this will be documented as a time finale.

Analgesia will be given according to the visual analog scale (VAS) once it is rated more than 4 by the patient at 2, 4, and 6 h for all patients irrespective of the type of anesthesia, and all participants will be discharged based on the post-anesthesia discharge scoring system (PADS) for determining home-readiness whereby the patient is judged fit for discharge when his score is ≥ 9 [22] and the 7th day assessment will be done after the patient is called back by the research assistants. Participants will be reassessed using the VAS on the 7th day postoperative. Diclofenac sodium 100 mg oral 8 hourly for 5 days will be considered as rescue analgesia postoperatively. All patients will be receiving a tablet of metronidazole 400 mg 8 hourly for the following five postoperative days.

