### Trial status

The first case was recruited on 2 December 2021, and as of 7 April 2022, 45 patients were registered out of the required sample size of 58 for this protocol version 3 as of 21 May 2022.

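### The principal investigator takes consent and also sees every allocation drawn from a half-A, half-B set of envelopes, so the next arm can be partly predicted at consent

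*Protocol article*

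**What the plan says.** All references are to the protocol article.

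- **Allocation.** Randomization and blinding describes envelopes of which "half of the envelopes will contain a chit with letter A while the other half will have a chit with letter B". Trained assistant researchers carry out the allocation. The envelope is opened when the patient is in theater, and blinding covers patients and outcome assessors. No number of envelopes and no blocks are given.
- **Size.** The abstract states that participants "will be randomized into two groups of 29 patients per arm". Trial status reports that "45 patients were registered out of the required sample size of 58" as of 7 April 2022.
- **Consent.** The Consent section says that a patient "will be consented to by the principal investigator at the time of screening for eligibility".
- **Recruitment.** Participant recruitment and study procedure says "Participants will be recruited from surgical outpatient by trained research assistants". It does not name who completes the screening log or who obtains the written consent it mentions.
- **Treatment.** The same section says "The local anesthetic mixture will be administered by the principal investigator as follows". After Fig. 1 it adds that both groups are prepared "before the beginning of open hemorrhoidectomy which will be done by the principal investigator".

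**The concern.** Drawing from a set with equal numbers of A and B means that each allocation changes the odds of the next. Anyone who knows the earlier draws can favor the arm with more envelopes left. The principal investigator is in that position, because giving one anesthetic and performing every operation reveals each patient's arm. That person also takes consent. Concealing the single envelope until theater does not break this link, because the prediction comes from counting past allocations.

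If the way consent is presented, or the decision to proceed, shifts even unconsciously with the expected arm, the groups can differ in disease severity or expected pain before treatment. The primary outcome is patient-rated pain in a small equivalence trial. Such a difference would enter the comparison directly, and blinding the assessors would not remove it.

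**Working it through.** **Inputs.** 29 per arm and 58 in total (abstract, Trial status); half A and half B (Randomization and blinding). The plan's own figures reproduce: Sample size determination states "a sample size of 26 participants per group was obtained which was increased to 29 participants in each arm", and 26/0.90 = 28.9, rounded up to 29, so 2 × 29 = 58.

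**Assumption.** The number of envelopes is not given. The base case takes it as 58 (29 A + 29 B). Larger pools are shown as a range.

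**Method.** Let each arm have m envelopes, and let the observer know the first k draws, of which a were A. Then

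P(a) = C(m,a) × C(m,k−a) / C(2m,k).

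Guessing the arm with more envelopes left is right with probability max(m−a, m−k+a) / (2m−k). Average this over a, then over the patients of interest.

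**Base case, m = 29.** The sum over all 58 draws has the closed form 29 + (2^58/C(58,29) − 1)/2 = 29 + (9.586 − 1)/2 = 33.29. That is 33.29/58 = 57.4%, or 4.3 more correct guesses than the 29 expected by chance.

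- First 29 patients: 52.9% correct.
- Last 13 patients (58 − 45, those outstanding on 7 April 2022): 67.9%.
- Allocations that are fully determined: 2m/(m+1) = 58/30 = 1.9 on average.

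**Delay between consent and allocation.** Consent precedes theater, so some consented patients may not yet be allocated. Suppose two are waiting (an assumption). The observer at patient t then knows t − 3 draws instead of t − 1. Correct guesses over the last 13 fall to about 64%, and fully determined allocations fall from 1.9 to about 0.4.

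**Pool size**, first 58 draws with no delay:

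| Envelopes | Correct overall | Correct, last 13 | Fully determined |
|---|---|---|---|
| 29 + 29 | 57.4% | 67.9% | 1.9 |
| 33 + 33 | 54.9% | 59.4% | under 0.01 |
| 58 + 58 | 52.1% | 53.3% | none |

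**Comparison.** The same calculation for fixed blocks whose length is known gives 70.8% for blocks of 4 and 68.3% for blocks of 6. Short fixed blocks would make matters worse.

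**The case against.** Several objections have force.

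- **Pool size.** The article never gives it. A reader might infer that the last allocations are certain. That follows only if exactly 58 envelopes were made and no consented patient is waiting. With 33 + 33 envelopes, certainty practically disappears.
- **Roles.** A reader might infer that the principal investigator also screens, or controls the theater list and can defer patients. The Consent section places this person's consent-taking at the time of screening; it does not say who screens. Nothing in the article gives this person control of the list. Assistants recruiting while the investigator consents can also be read as a division of labor, not a contradiction. Control of consent is enough for the concern.
- **Size of bias.** A reader might want to turn predictability into VAS points and compare it with the 0.73 used in the sample size calculation. That needs an assumed shift in patients' expected pain, and an assumption about how sure the investigator must be before acting. The article supports neither. For example, shifting expected pain by plus or minus g at every guess, even near-even ones, gives a bias of about 0.30 × g. Acting only at 60% certainty or more gives 0.20 × g.
- **Room to select.** Hospital records gave about 33 cases in 6 months, which suggests little slack for turning patients away. This is only partly reassuring, as 45 were registered by 7 April 2022.
- **Condensed article.** Details of sequence generation may sit in the full protocol. The balanced envelopes and the investigator's overlapping roles, however, are positive statements and not omissions.
- **Adjustment.** The analysis section names unadjusted comparisons but does not rule out adjustment in an analysis plan that is not shown. The point does not rest on this.

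**Conclusion.** The concern holds in a limited form. The article has one unblinded person take consent and learn every allocation from a balanced set, so the next arm is partly predictable at consent. If there are 58 envelopes, predictability is 57% overall and about 68% over the last 13 patients (about 64% with two patients waiting). It falls to about 55% overall with 33 + 33 envelopes and 52% with 58 + 58. The risk is moderate and mostly late. The calculations show opportunity, not that selection took place, and they give no estimate of bias in the pain comparison. Stating the number of envelopes would settle which row of the table applies.

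**What to change.** 1. **Consent.** Amend the Consent section so that eligibility and consent are settled and logged, before theater, by recruiting assistants who neither open envelopes nor learn earlier allocations. Randomization and blinding gives allocation to assistant researchers, and nothing separates them from the recruiters, so name different assistants for the two tasks. Reconcile Consent, Randomization and blinding, and Participant recruitment and study procedure on who does what.
2. **Allocation of patients not yet entered.** Use a computer-generated list prepared by the biostatistician, in sequentially numbered, opaque, sealed envelopes, without short fixed blocks. Alternatively, fill the pool well beyond need, for example 58 A and 58 B. State the number of envelopes used so far.
3. **Patients already entered.** Report degree of hemorrhoids, ASA level, age and gender by arm, separately for early and late recruitment. These variables are already collected.

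**Cost.** Step 1 needs wording and a clear split of duties; whether present staff suffice is for the sponsor to confirm. Step 2 needs one list and re-packed envelopes, and the arms may not end at exactly 29/29. Under simple randomization of all 58, the SD of an arm's size would be √(58 × 0.25) = 3.8 patients. For 13 patients it is √(13 × 0.25) = 1.8. Step 2 can reach at most the 13 not registered on 7 April 2022, and fewer by the version date of 21 May 2022. Step 3 remains feasible even if recruitment has closed.

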## Methodology

### Study design

This study will be a prospective equivalence randomized, double-blind controlled trial conducted in the department of surgery at Kampala International University Teaching Hospital (KIU-TH), western Uganda.

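### The trial is called double-blind and patients are said to be blinded, but the two anesthetic procedures can be told apart by an awake patient, no masking step is described, and the patient rates the primary outcome

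*Protocol article*

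**What the plan says.** The Study design section of the protocol article states: "This study will be a prospective equivalence randomized, double-blind controlled trial". The title and the abstract's Methods paragraph use the same label. Randomization and blinding says who is masked: "the patients and outcome assessors will be blinded about the anesthesia". The same section says when the allocation is revealed: "The content of the envelope will be opened once the patient is in the theater".

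Participant recruitment and study procedure then describes both techniques step by step.

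- Local anesthesia (group A): "Group A patients, in lithotomy or prone jack-knife positions, will be infiltrated with bupivacaine 0.5" percent. Two injections come first, and then "further 4 injections will be administered into 4 quadrants performing a diamond shape". As to who gives them: "The local anesthetic mixture will be administered by the principal investigator as follows".
- Saddle block (group B): "For group B patients, the back will be cleaned with 70% alcohol and draped while in a sitting position". Lidocaine is put into the skin, a 25-G spinal needle is passed at L4/L5 by an anesthetist or anesthesiologist, and the bupivacaine is given. Then: "The patient will be kept in the sitting position for 10 min and thereafter placed in supine".

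Primary outcome variable defines the endpoint as the AUC of a 0 to 10 VAS for pain, read at 2, 4 and 6 hours and at 7 days. The procedure section makes clear that the patient gives the VAS rating, and that research assistants separate from the recruiting team collect it. The Unblinding section sets a criterion for outcome assessors only.

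**The concern.** Calling a trial double-blind, and naming patients among those blinded, tells the reader that a patient's expectations about the technique cannot shape the patient's pain score. For a subjective endpoint this is one of the main protections a randomized design offers. If patients can recognise their arm, the protection is absent, however well the data collectors are masked.

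The matter is sharper in an equivalence trial. A reporting shift linked to knowledge of the arm could widen a true difference, create one, or cancel one and make the arms look alike. Because a VAS rating above 4 also leads to analgesia, knowledge of the arm could affect analgesic use and, through it, later readings.

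Study limitations does not mention blinding, while Study strengths describes the result as level 1 evidence. A reader would have no prompt to discount for this.

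**Working it through.** No arithmetic settles this point, and the sample size calculation does not bear on it. The check sets the blinding statement beside the procedures and the outcome definition.

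**1. What a patient experiences, by arm (Participant recruitment and study procedure).**

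| Feature | Local anesthesia (A) | Saddle block (B) |
|---|---|---|
| Position while anesthetized | lithotomy or prone jack-knife | sitting |
| Skin preparation specific to the technique | none on the back described | back cleaned with alcohol and draped |
| Injection site | perianal | lower back, L4/L5 |
| Injections | 2 + 4 = 6 perianal | lidocaine skin infiltration, then one spinal needle |
| Given by | principal investigator | anesthetist or anesthesiologist |
| Period seated after injection | none described | 10 minutes |
| Position for the operation | lithotomy | lithotomy |

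Only the last row is the same in both arms. Site and position alone are enough for an awake patient to distinguish them.

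**2. Is the patient awake?** The article does not say so outright. Three details point that way: group B patients must sit for 10 minutes after the injection; the effect of the anesthetic is confirmed before surgery in both groups; and Ancillary and post-trial care and Trial discontinuation both foresee conversion from local anesthesia because of too much pain. No sedation is mentioned.

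**3. Is any masking step described?** A sham back puncture in group A, a sham perianal infiltration in group B, or sedation would belong in this same sequence. The text gives needle gauge, injection depths, antiseptic and time seated, but none of these.

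**4. Who rates the primary outcome?** The patient scores the VAS, and the AUC is built from those scores. The research assistants collect them. Their blinding is plausible and nothing in the article refutes it, but it protects the recording of the score and not the score itself. This holds equally for the day 7 review, in person or by telephone.

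**5. Can the bias be sized?** No. The document gives no estimate of how far knowledge of the technique moves a pain score, nor in which direction.

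**The case against.** The strongest reply is that this is a condensed article. The flow chart and the SPIRIT figure are not available in the text reviewed, and a full protocol might explain how patients are masked. Nowhere does the article state that no sham or sedation is used; that is inferred from silence. This stands, and it limits the wording: the described steps appear incompatible with patient blinding, and no masking step is described. It does not remove the point, because the article makes the blinding claim and sets out in detail procedures that do not support it.

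A reader might go further in four ways that the documents do not support.

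- **That patients certainly knew their arm.** The text shows that they could know it. A masking step used but not reported cannot be excluded.
- **That the unblinded operator is a second contradiction.** The principal investigator gives the local anesthetic and operates, but Randomization and blinding claims masking only for patients and outcome assessors. An unblinded operator refutes nothing stated there.
- **That the investigator's withdrawal decisions compromise the primary analysis.** Data processing and analysis plan analyses all randomized patients by intention to treat as well as per protocol. Membership of the first set does not depend on those decisions. Failure of the anesthetic is also judged in theater, where a decider unaware of the arm may be unworkable.
- **That the bias would consume a stated share of the margin.** Any numerator would be invented. The 0.73 in Sample size determination is a difference in mean pain scores from an earlier trial, whereas the primary outcome is an AUC over four readings, so the two are not on the same scale.

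**Conclusion.** The point holds as an inconsistency between a stated design property and the procedures described. On the article's own text, patients can tell which anesthetic they received, and they are the raters of the primary outcome. The double-blind label and the statement that patients are blinded are therefore unsupported; blinding of the data collectors remains credible.

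This rests on two inferences: that patients are awake during the anesthetic, and that the absence of any sham or sedation from a detailed description means none was used. Both fit the text, and neither is stated in it. The effect on the result has no derivable size or direction. The consequence is for how the pain comparison and any equivalence conclusion may be described and read, not for the sample size.

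**What to change.** If a masking method was actually used, describe it under Randomization and blinding. If not:

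1. In the title, abstract and Study design section, replace the double-blind label with: outcome data collectors blinded; patients and operator not blinded.
2. Under Randomization and blinding, delete the claim that patients are blinded and keep the claim for outcome assessors.
3. Under Study limitations, add that pain is self-reported by patients who can know their arm, and that this limits the equivalence conclusion.

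The cost is wording only, plus a less favorable design label. Treatment, assessments and sample size do not change, and the edits remain possible at any stage of recruitment.

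A new question asking patients at 6 hours to guess their arm is not worth requiring. Trial status reports 45 of 58 patients already registered by 7 April 2022, which leaves at most 58 − 45 = 13 of the planned number still to be registered, and the answer would add little from patients who can recognise the procedure.
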